## Methods

### Study design

This randomized, double-blind, controlled clinical trial evaluates the efficacy of combining HD-tDCS with AE to improve cognitive function in individuals with CIAS. Eligible participants will be randomly assigned to one of four groups in equal proportions (1:1:1:1): MRI-guided HD-tDCS +AE (Group 1), MRI-guided HD-tDCS alone (Group 2), AE alone (Group 3), and a control group (Group 4). Assessments will be conducted at baseline (T0), at 2 weeks (T1), at 4 weeks (T2), and at 6 months post-intervention (T3). The specific intervention measures for each group are delineated as follows: the MRI-guided HD-tDCS + AE group first undertakes a 15-minute warm-up exercise. Subsequently, HD-tDCS and AE treatments are administered concurrently for a duration of 30 minutes. The HD-tDCS group receives 30 minutes of electrical stimulation per session. The AE group’s intervention comprises a 15-minute warm-up followed by a 30-minute formal AE stage, amounting to a total of 45 minutes. The control group does not receive HD-tDCS or AE but instead is provided with routine psychiatric care, including regular psychiatric follow-ups, medication management, and general health guidance, but no experimental interventions. Each intervention for the aforementioned groups is conducted once daily, five days a week, over a period of four weeks, culminating in a total of 20 sessions. The study design is illustrated in **Figure 1**.

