### Randomization

The randomization process will be conducted by an independent researcher who is not involved in the experiment. This researcher will utilize a random number table to randomly allocate participants into four distinct groups, labeled as “1, 2, 3, and 4.”. Specifically, the group coding is as follows: Group 1 corresponds to the HD-tDCS combined with AE group, Group 2 to the HD-tDCS group, Group 3 to the AE group, and Group 4 to the control group. The random allocation process will be implemented using Microsoft Excel 2019. Upon the recruitment of all 48 eligible participants, each individual will be assigned a unique identifier and paired with a randomly generated value using Excel’s “=RAND ()” function. The “Paste Special” function will then be employed to convert these random numbers into fixed values. Subsequently, the list of participants will be sorted in descending order based on the random values, with participants allocated to groups 1 to 4, each comprising 12 individuals, according to their ranking positions. Once the randomization scheme is established, it will be sealed within an opaque envelope, which will be opened sequentially in accordance with the order of subject enrolment. The allocation scheme contained within each envelope will dictate the group assignment for the corresponding participant. This approach ensures that researchers are unable to access the randomization scheme in advance, thereby safeguarding the integrity of the randomization process.

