All researchers involved in data management and statistical analysis will remain blinded to the grouping information throughout the entire process. Specifically, data will be analyzed using coded group identifiers (e.g., Group A, B, and C), and the blinding code will remain undisclosed until the completion of the statistical analysis and the locking of the database. This procedure aligns with the principle of the blind method for minimizing assessment bias, as outlined in clinical trial protocols (46).

A Blinding Integrity (BI) assessment will be conducted following the final intervention session. Participants will be required to specify their perceived group allocation via a forced-choice questionnaire, asking: “Which intervention do you believe you received?” The response options will include (1): Combined HD-tDCS and AE (2), HD-tDCS alone (3), AE alone (4), Control, or (5) Unsure. To rigorously assess the blinding effect, Bang’s Blinding Index (BI) will be calculated for each group. This index allows for the distinction between genuine unblinding and random guessing. The BI is the primary tool for quantitatively evaluating the effectiveness of blinding implementation in clinical trials. By calculating the BI separately for each group, we can accurately assess the maintenance of blinding across different intervention groups (47).

Unlike drug trials, these trials—such as those involving surgery, rehabilitation, psychological, and physical therapy—cannot physically blind the “treatment itself” (48). During the informed consent process, we informed participants that the study was designed to investigate the effects of non-pharmacological interventions on cognitive function of individuals with schizophrenia. In the informed consent form, all intervention measures were described as “interventions with potential benefits,” without disclosing which group was the experimental group and which was the control group.The language used in the informed consent form was intentionally general to avoid revealing specific differences between groups, thereby minimizing the expectancy effect. Upon completion of the study, it is imperative to fully disclose the actual research design and the group assignments to all participants.

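### Bang's Blinding Index is applied to a four-arm guess without adaptation, so in its usual form it does not separate unblinding from random guessing and would understate partial unblinding

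*Protocol article*

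**What the plan says.** The Blinding section of the protocol article plans a check after the last intervention session: "Participants will be required to specify their perceived group allocation via a forced-choice questionnaire". The answers on offer are the four trial arms and Unsure. The analysis is then fixed: "To rigorously assess the blinding effect, Bang’s Blinding Index (BI) will be calculated for each group". Two claims are made for it. The first is "This index allows for the distinction between genuine unblinding and random guessing". The second is "By calculating the BI separately for each group, we can accurately assess the maintenance of blinding across different intervention groups".

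The section gives no formula, no reference value and no collapsing of the four arms into two categories, and it names no multi-arm version of the index. Study design sets equal allocation to the four arms, and Randomization sets 12 participants per arm. The limitations in the Discussion acknowledge that there is neither sham stimulation nor sham exercise.

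**The concern.** The index in its usual form sets correct guesses against incorrect ones as if the two were equally likely by chance. That is so when there are two arms to choose from. With four arms, a participant who knows nothing is right about one time in four, so pure guessing pulls the index well below zero, and a value near zero already reflects guessing better than chance.

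Read on the customary scale, pure guessing would look like systematic wrong guessing, and moderate unblinding would look like successful blinding. The index is the only quantitative blinding check that the article describes, in a trial labelled double-blind that concedes incomplete participant blinding. A check on that weakness should not lean towards reassurance.

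**Working it through.** **Inputs**
- Four arms, equal allocation (Study design): chance of naming the right arm under even guessing = 1/4 = 0.25.
- Planned participants per arm: 12 (Randomization).
- Answer options: four arms plus Unsure (Blinding).
- Share answering Unsure, u: not given; assumed range 0 to 0.5.
- Formula for the index: not given; the usual per-arm form is assumed.

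The article states no index value or threshold, so there is no figure of its own to reproduce.

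**Step 1. The index.** BI = (correct - incorrect)/(correct + incorrect + unsure) = (2p - 1)(1 - u), where p is the share correct among those who name an arm.

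**Step 2. Value under random guessing with K arms offered.** Here p = 1/K, so BI = (2/K - 1)(1 - u). At u = 0:
- K = 2: 2/2 - 1 = 0
- K = 3: 2/3 - 1 = -0.33
- K = 4: 2/4 - 1 = -0.50

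**Step 3. Effect of Unsure answers at K = 4.** BI = -0.5(1 - u):
- u = 0: -0.50
- u = 0.2 (all five options equally likely): -0.40
- u = 0.5: -0.25

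**Step 4. What an index of 0 means.** BI = 0 requires 2p - 1 = 0, so p = 0.5 = 2 × 0.25. This holds for every u below 1.

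**Step 5. Size in one arm of 12, nobody unsure.** The last column is the exact binomial probability of at least that many right under even guessing.

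| Right of 12 | BI = 2p - 1 | P(at least this many, p = 0.25) |
|---|---|---|
| 3 | -0.50 | 0.61 |
| 6 | 0.00 | 0.054 |
| 7 | 0.17 | 0.014 |
| 8 | 0.33 | 0.003 |

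For 7 of 12, the standard error is √(4 × 0.583 × 0.417/12) = 0.285. The Wald 95% interval is 0.167 ± 1.96 × 0.285 = -0.39 to 0.72. It includes 0, so on the usual scale the arm would not stand out.

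**Step 6. Uneven guessing.** Suppose guesses ignore the true arm but favour one answer, with shares 0.7, 0.1, 0.1 and 0.1. The per-arm values are 2(0.7) - 1 = 0.4 and 2(0.1) - 1 = -0.8 three times. Their mean is (0.4 - 2.4)/4 = -0.5. The average over arms keeps its random-guess value, but single-arm values move a long way with nobody unblinded.

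**Step 7. The same test for a rescaled index.** (4p - 1)/3 is 0 at 3 of 12, 0.33 at 6 of 12 and 0.44 at 7 of 12. Under the uneven pattern of Step 6 it gives (2.8 - 1)/3 = 0.6 in the favoured arm and (0.4 - 1)/3 = -0.2 in the others. Rescaling alone therefore does not settle the question arm by arm. Comparing arms does: the favoured answer is given by 0.7 of those in that arm and 0.7 of those outside it, a difference of 0.

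**The case against.** The best defence is that the article never prints a null value of 0 and sets no rule for calling an arm well blinded. A reader might infer that the plan defines 0 as random guessing and will report an arm at twice chance as blinded. The text does not go that far. The coding of the index, or a collapsing of answers, could also stand in the full protocol or analysis plan. This stands as a limit on what may be said about the authors' intent. It does not rescue the sentence on random guessing, which is stated without qualification for a four-choice form and is untrue of the index in its usual form.

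Second, the damaging case may be rare. Without sham, participants either cycle or do not, and either wear electrodes or do not. If nearly all name their arm correctly, p is close to 1 and, with few Unsure answers, the usual and the rescaled index both approach 1. This stands too: the error matters only for partial guessing.

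Third, a reader might infer that the efficacy claim depends on this index, or that the control arm would be worst affected. Nothing in Statistical methods uses the index, and no passage singles out the control arm. The incomplete blinding and the possible expectancy effect are conceded whatever the index shows.

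Fourth, 6 of 12 right has probability 0.054 under even guessing, so an index of 0 in a single arm is not strong evidence of unblinding. That is correct. The 7 of 12 case is the clearer illustration.

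**Conclusion.** The stated property of the index does not hold for the planned question if the index is used in its usual form. Random guessing among four equally likely arms gives about -0.5(1 - u), and 0 corresponds to twice chance. Read on the usual scale, the index would understate partial unblinding, as the 7 of 12 case shows.

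This rests on the usual formula, on no adaptation being specified elsewhere, and, for the single-arm values, on guesses spread evenly over the arms. The result that 0 means half right among those naming an arm needs neither even guessing nor a value for u. The consequence is confined to the blinding check; the primary outcome, effect estimates and sample size are untouched. Severity: minor.

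**What to change.** Keep the questionnaire and change its analysis:

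1. Report the full table of true arm by answer, including Unsure.
2. Use a chance reference for four choices, for example (4p - 1)/3 per arm, with an exact interval for p set against 25%. State the Unsure share alongside, since p leaves those answers out.
3. Because uneven guessing shifts single-arm values, also compare, for each arm, the share naming it among participants in that arm with the share naming it in the other three arms.
4. Reword the sentence that says the unadapted index separates unblinding from guessing.

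The cost is a few sentences and a slightly longer analysis of data already being collected. With 12 per arm the intervals will be wide, and the report should say so.

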### MRI-guided high-definition transcranial direct current stimulation intervention

To construct precise and anatomically accurate head models, T1- and T2-weighted MRI data will be collected to optimize electrode placement and account for individual anatomical variations. These models will be developed and simulated using SimNIBS software to estimate the electric field distributions resulting from HD-tDCS stimulation. Eight distinct 4*1 montages centered on the mPFC will be used to simulate 280 the E-field for each brain. The finite element method will be utilized to compute the normal component of the induced electric field. The head models, derived from individual MRI data will differentiate among five tissue types: skin, skull, cerebrospinal fluid, gray matter, and white matter. The mPFC will be delineated in each participant’s brain according to the Ranta atlas. The study will utilize an MRI-guided HD-tDCS device (MxN-9-9002A, Soterix Medical, New York, USA). We used five small circular electrodes (1×1 cm each) with a small area for high-precision electrode arrangement, concentrating the stimulation current on the target brain region. Specifically, the central electrode (anode) will be placed in the mPFC (fz) according to international 10–20 system, while the four surrounding cathodes will be directly located in front of Fp1, Fp2, F7, and F8, thus forming a circular current circuit. The current intensity will be maintained at 2 mA. Each HD-tDCS session will involve the delivery of a 2mA direct current for a duration of 30 minutes, with ramp-up and ramp-down periods of 30 seconds each. HD-tDCS will be administered once daily for 30 minutes, five times a week over a total duration of 4 weeks, culminating in 20 treatment sessions.

### Aerobic exercise

AE training will be administered using a stationary bicycle. The training sessions will be characterized by moderate to low intensity and will include both a warm-up phase and a formal AE phase. Each session is customized according to each individual’s maximum heart rate (HRmax), which is calculated using the formula: HRmax = (220 - Age) × 0.7. (34). Each session will last for 45 minutes, comprising a 15-minute warm-up and a 30-minute formal AE phase. During the warm-up, participants’ heart rates are expected to remain between 55% and 60% of HRmax. In the formal AE phase, heart rates should be maintained between 60% and 70% of HRmax (34). A portable monitor will be utilized to record heart rates throughout the training, ensuring participants maintain an appropriate level of physical exertion. Blood pressure measurements will be taken both before and after the sessions. The intervention will occur once daily, 5 days per week, over a period of 4 weeks, culminating in 20 treatment sessions.

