**Trial registration details:**

The study is registered with https://www.chictr.org.cn/ protocol registration number ChiCTR2500106980 (date of registration: 1. August. 2025). It was approved by the Research Ethics Committee of the Second Affiliated Hospital of Xinxiang Medical University (Approval Code: XYEFYLL-2025-16, Approval Date: 17 February 2025). Recruitment began in December 2025.

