### Blinding

All participants and researchers will remain blinded throughout the research process. During the entire research process, the designated stimulus conditions will be kept strictly confidential and will only be disclosed to the principal researcher. Four distinct groups will be tasked with administering the treatment, with strict measures in place to prevent inter-group communication regarding the particulars of each treatment. Each group will be informed only of its own treatment protocol and will remain unaware of the grouping details or the treatment plans of the other groups. The principal investigator will assign specific measures to each group, which will then implement the experimental treatment for their respective patient cohorts. Patients will remain unaware of their group allocation and will be instructed not to discuss the grouping, the treatment received, the completion of questionnaires, or any other aspects of the experimental protocol. During the phase of result measurement, personnel involved in data collection and analysis will also be blinded to the grouping information and specific measures. Subsequently, the principal investigator will conduct two unblinding procedures: the first will occur before data locking, and the second will follow data analysis. The initial unblinding will occur after data locking, organizing the data into groups 1–4 without disclosing the actual correspondence between these groups and their respective identities. The second unblinding will take place after the data analysis, explicitly revealing the specific identities of groups 1-4. Furthermore, to ensure that participants are unaware of their group assignments, the intervention activities will be conducted in designated rooms. Although the researchers will be aware of the group assignments, they must not disclose this information to the participants and will not be involved in the evaluation or analysis of the study. Additionally, the evaluators and data analysts will remain unaware of the intervention group’s situation throughout the entire research process.

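### The aerobic exercise formula labels 70% of (220 − Age) as the maximum heart rate, so the intended training intensity cannot be determined

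*Protocol article*

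**What the plan says.** The Aerobic exercise section of the protocol article describes stationary cycling: a 15-minute warm-up, then a 30-minute formal phase. It characterises the intensity once, in words: "The training sessions will be characterized by moderate to low intensity". Each session is adjusted to the participant's maximum heart rate, "which is calculated using the formula: HRmax = (220 - Age) × 0.7".

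Two bands are defined on that quantity. In the warm-up, "heart rates are expected to remain between 55% and 60% of HRmax". In the formal phase, "heart rates should be maintained between 60% and 70% of HRmax". On monitoring, the section says "A portable monitor will be utilized to record heart rates throughout the training".

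The same prescription serves Group 1 (HD-tDCS plus exercise) and Group 3 (exercise alone). The article gives no target in beats per minute, no workload, no perceived-exertion target and no second definition of HRmax.

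**The concern.** A quantity called the maximum heart rate should not already contain a training fraction. Multiplying (220 − Age) by 0.7 gives a submaximal target rate. Taking 55–70% of that applies an intensity fraction twice.

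There are two ways to read the text:

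- **The 0.7 is a slip.** It equals the upper limit of the formal band (70%), so a target-rate formula may have been printed where the formula for the maximum belonged. The formal phase is then 60–70% of (220 − Age).
- **The lower targets are meant.** The label HRmax is then wrong, and the formal phase is 42–49% of (220 − Age).

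Heart rate is the article's only measurable intensity target for the exercise factor. If its definition is wrong, a reader cannot say what exercise dose the trial tests, and another centre could not reproduce it. The Background and Discussion attribute the expected benefit to physiological effects of exercise such as BDNF release and cerebral blood flow, so the intended intensity matters for interpreting either a positive or a null result.

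**Working it through.** **Inputs.** The formula and both bands come from the Aerobic exercise section. The age limits, 18 and 55, come from the Eligibility criteria; age 40 is added as an intermediate point. The article states no bpm figure, so there is no printed result to reproduce.

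**Step 1: the printed HRmax.** 0.7 × (220 − Age):

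- Age 18: 0.7 × 202 = 141.4 bpm
- Age 40: 0.7 × 180 = 126.0 bpm
- Age 55: 0.7 × 165 = 115.5 bpm

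**Step 2: the literal bands as shares of (220 − Age).**

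- Warm-up: 0.55 × 0.7 = 0.385 to 0.60 × 0.7 = 0.42
- Formal: 0.60 × 0.7 = 0.42 to 0.70 × 0.7 = 0.49

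**Step 3: both readings in bpm.**

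| Age | 220 − Age | Literal warm-up | Literal formal | Warm-up if 0.7 is a slip | Formal if 0.7 is a slip |
|---|---|---|---|---|---|
| 18 | 202 | 77.8–84.8 | 84.8–99.0 | 111.1–121.2 | 121.2–141.4 |
| 40 | 180 | 69.3–75.6 | 75.6–88.2 | 99.0–108.0 | 108.0–126.0 |
| 55 | 165 | 63.5–69.3 | 69.3–80.85 | 90.8–99.0 | 99.0–115.5 |

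The upper limit in the last column equals the printed HRmax of Step 1 at each age. This is what makes a slip plausible.

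**Step 4: distance between the two formal bands.**

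- Lower limits differ by (0.60 − 0.42) = 0.18 of (220 − Age): 36.4, 32.4 and 29.7 bpm at ages 18, 40 and 55.
- Upper limits differ by (0.70 − 0.49) = 0.21 of (220 − Age): 42.4, 37.8 and 34.65 bpm.
- The gap from the top of the literal band to the bottom of the other is (0.60 − 0.49) = 0.11 of (220 − Age): 22.2, 19.8 and 18.15 bpm.

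Because 0.49 is below 0.60, the bands are disjoint at every age. The literal formal phase (at most 49%) even lies below the warm-up on the other reading (at least 55%).

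**Step 5: does other text settle it?** No. The Study design section gives durations only. The verbal description of intensity does not decide between the readings. The monitor shows what rate was reached, not what rate was intended.

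**The case against.** The strongest reply is that the text is not indeterminate. Formula, bands and durations give one computable range for any age, so the prescription is fixed as printed and the fault is only a label. It is true that a range can be computed. But doing so means accepting as a maximum something that is not one, so either the formula or the label has to change. What remains unknown is the intended dose.

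A second reply is that the article never states that 220 − Age is the age-predicted maximum, and that the source cited for the formula is not available here. That limits what can be said about which reading is right, and no choice is made between them here. It does not rescue a definition that multiplies by 0.7 and calls the result a maximum. One can also argue that 69–81 bpm at age 55 is an implausible target for a cycling phase, so that a stray 0.7 is the natural explanation. That may well be so, but it is an inference, and it too ends in a correction of the formula.

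Third, the consequences are limited, and this stands. The error does not touch the sample size or the analysis model. Both exercise arms share one prescription, and the Blinding section says "The principal investigator will assign specific measures to each group", so nothing suggests that Groups 1 and 3 would be dosed differently. Because heart rates are recorded, the delivered dose can be recovered afterwards.

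**Conclusion.** The concern holds. The quantity labelled HRmax is 70% of (220 − Age), and the literal formal band is 42–49% of (220 − Age). If the 0.7 is a slip, the intended formal band is about 30–42 bpm higher, depending on age and on which limit is compared, with 18–22 bpm of clear space between the two bands at the ages checked.

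The bpm figures are pure arithmetic on the printed formula. That the label is wrong rests on the usual understanding of 220 − Age as the age-predicted maximum. That the 0.7 is a slip is a conditional reading, not a finding.

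The damage is confined to the specification of the exercise dose in Groups 1 and 3: its interpretation and its reproducibility. It should be fixed, but it does not threaten the validity of the randomised comparison.

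**What to change.** The sponsor should confirm the intended intensity from the source of the formula and then do one of the following:

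- **(a)** define HRmax as 220 − Age and keep the bands at 55–60% and 60–70%; or
- **(b)** if the lower targets are meant, drop the HRmax label and state the bands as 38.5–42% and 42–49% of (220 − Age).

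In either case, give the therapists one bpm table by age, used identically in Groups 1 and 3, and report achieved heart rate as a percentage of (220 − Age) from the monitor data already planned.

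If anyone has already trained, check which band was applied. The trial registration details state "Recruitment began in December 2025", but the Randomization section places allocation at this point: "Upon the recruitment of all 48 eligible participants". Training may therefore not have begun, and the correction may still come in time.

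The cost is one corrected line and one short table, with no new measurement.
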